### **7.5.2 Other Safety Assessments**

For clinical laboratory parameters and vital signs assessments pre-specified in the protocol, summary statistics for continuous parameters will be presented for Day 0 pre- and post-vaccination time points, and for the change from pre-vaccination to post-vaccination assessment, by treatment group and study group.

## **7.6 Sample Size Considerations**

The sample sizes were selected because they are judged to be adequate for safety evaluations. A sample size of 1392 MVA85A/AERAS-485 subjects will give a greater than 75% chance of observing an adverse event that has an approximately 1 in a 1000 actual rate of occurrence. A sample size of 165 MVA85A/AERAS-485 subjects in the safety cohort will provide an 80% chance of observing at least one adverse event which has an approximate 1% actual rate of

occurrence. Given a tuberculosis cumulative incidence of 3% over 18 months in the control group, 1392 subjects per treatment group (2784 subjects total) would be required to demonstrate positive efficacy when the true efficacy of MVA85A/AERAS-485 is approximately 60%. An estimate of 7.5% of subjects lost to follow-up in each treatment group is assumed over 18 months. Calculations are based on a two-sided log-rank test at a significance level of 0.05. Calculations assume 90% power to detect a 60% reduction in tuberculosis rate between the MVA85A/AERAS-485 and control groups; given an estimated enrollment over 21 months, the last subject to enroll in the study will be followed for a minimum of 15 months to maintain statistical power.

However, delays in recruitment and/or a lower TB incidence may result in a need to extend follow-up to preserve the power of the study to detect a treatment group difference. To assess the possible impact of departures from planned subject recruitment rate, total number of TB cases accrued, loss to follow-up, or proportional hazards assumptions, an independent statistician not involved with the conduct or analyses of the trial will perform a sample size review using an interim pooled estimate of the TB event rate and the original treatment effect. It is critical that this interim review occur when sufficient TB events have accrued, to allow for a stable estimate, but before the total cohort has been recruited, due to trial management issues. The initial sample size review is proposed to occur while enrollment is ongoing but when approximately 30% of expected events have accrued, but no later than before 75 percent of the total cohort has been recruited. Details of this review and analysis will be documented in a statistical analysis plan, finalized prior to the review, and in the SMC charter. Timing of subsequent reviews will be determined based on planned completion of recruitment closure after 21 months and enrollment rate.

These reviews will not result in a statistical penalty as no treatment comparisons will be performed. The monitoring of these parameters and possible courses of action will be detailed in a separate statistical analysis plan and in the SMC Charter. Further reviews and/or unblinding by the SMC to treatment assignments will be performed at the discretion of the SMC if, based on their judgment, additional information is warranted to better assess ongoing event rates to achieve the endpoint of the study.

The SMC mandate, oversight schedule, and membership will be delineated in the SMC Charter. The statistical analysis plans to be prepared for all analyses will be approved by the SMC. Aeras and study site personnel will remain blinded to treatment assignments and interim analyses by-treatment results throughout the study.

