#### **5.1.5 Safety Monitoring Committee**

If study vaccine administration is paused by the principal investigator, the local medical monitor, or the global medical monitor, an SMC will be convened. The SMC is composed of five voting members (two licensed physicians from South Africa, one licensed physician from the United Kingdom, and two licensed physicians from the US) and may have up to two alternate physician members. The voting members can not be directly involved with the conduct of the study, can not be employees of Aeras and must be experienced in the evaluation of adverse events in clinical trials. The SMC will also have a non-voting statistician and a non-voting Aeras member who will record committee actions.

The SMC will convene to review safety data when the last subject in the Safety Cohort (Study Group 1) completes Study Day 84. The SMC will evaluate blinded and unblinded-by-group safety data to determine if a pattern of adverse events related to MVA85A/AERAS-485 or other safety or risk concerns exist. Only the SMC and the independent statistician responsible for preparing these analyses would be unblinded during these reviews. If such a pattern

exists, the Safety Monitoring Committee will determine if additional subjects will be entered into this safety group for additional safety determination or if further studies need to be performed. The SMC will conduct a second unblinded-by-group safety and risk review after the 1000th infant completes the Study Day 84 visit. The SMC may also review an individual SAE or it may choose to review adverse events, serious adverse events, solicited adverse events, and laboratory and vital signs data. The SMC may unblind any amount of safety information needed to conduct their assessment. All procedures associated with this review, including objectives, data handling, and elements to be included for review will be documented in SMC minutes.

Based on its review and the protocol stopping rules (Section 6) the SMC will make recommendations in the SMC minutes to Aeras regarding further conduct of the study and further administration of study vaccine. The conclusions of the SMC will be communicated to the investigators and the IRB/Ethical Committees and the national regulatory authority for their information. The sponsor agrees to abide by the decision of its SMC.

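### Section 7.6 permits discretionary by-arm unblinding for event-rate purposes with no alpha provision or bar on its use to extend follow-up, and 5.1.5 conflicts with 7.6 on the sponsor's blind

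*Protocol*

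**What the plan says.** Protocol section 7.6 sizes the efficacy comparison as follows: "Calculations are based on a two-sided log-rank test at a significance level of 0.05". It says follow-up may have to be lengthened if recruitment is slow or TB incidence is low, and gives an independent statistician the task of reviewing the pooled TB rate against the original effect size, first at about 30% of expected events. On those reviews it states: "These reviews will not result in a statistical penalty as no treatment comparisons will be performed".

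Later in the same paragraph it goes further: "Further reviews and/or unblinding by the SMC to treatment assignments will be performed at the discretion of the SMC". The condition is that the SMC thinks more information is needed to assess how event rates are running so that the endpoint can be reached. Courses of action are referred to a separate analysis plan and the SMC Charter. The section also says: "Aeras and study site personnel will remain blinded to treatment assignments and interim analyses by-treatment results throughout the study".

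Section 5.1.5 bars Aeras employees from voting membership and then adds: "The SMC will also have a non-voting statistician and a non-voting Aeras member who will record committee actions". In describing the by-group safety reviews, it limits unblinding to the SMC and the independent statistician who prepares the analyses. It makes no exception for the Aeras member and mentions no closed session.

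**The concern.** There are two separate defects.

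First, the argument for no penalty is that the arms are not compared. That argument fails once treatment assignments are opened for TB events. The purpose named in 7.6 is power, not safety; 5.1.5 already lets the SMC unblind whatever safety information it needs, so the 7.6 sentence adds access for efficacy event rates. Follow-up length is a real lever: 7.6 leaves further extension open without a cap, and the change list in 12.6 records that six months have already been added. If a committee that has seen TB by arm can influence whether follow-up goes on, the unadjusted log-rank test no longer holds its 5% level.

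Second, 5.1.5 and 7.6 cannot both be taken literally. If the SMC is unblinded and a sponsor representative is on it, the sponsor is not blinded throughout. A sponsor blind that the protocol itself contradicts is hard to defend when the efficacy result is read.

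**Working it through.** **Inputs from section 7.6.** Two-sided log-rank test at 0.05; control incidence 3% over 18 months; 60% reduction (hazard ratio taken as 0.4); 1392 per arm; 7.5% loss over 18 months; stated power 90%.

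**Step 1: reproduce the stated power.** Take exponential event and dropout hazards.
- Control event hazard: −ln(0.97)/18 = 0.001692 per month. Vaccine-arm hazard: 0.4 times that. Dropout hazard: −ln(0.925)/18 = 0.004331 per month.
- Probability of an observed event by 18 months: λ/(λ+η) × (1 − exp(−18(λ+η))). This gives 0.02887 (control) and 0.01165 (vaccine).
- Expected events: 1392 × (0.02887 + 0.01165) = 56.4.
- Freedman power: Φ(√56.4 × 0.6/1.4 − 1.96) = Φ(1.26) = 0.896.

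This agrees with the stated 90%, so the planning figures are sound and are not in dispute.

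**Step 2: pooled reviews.** If the decision to extend does not depend on the arm difference, the final statistic is still standard normal under the null. A simulation of 2 million null trials, each extended at random, gave a two-sided error of 0.0497, which is 0.05 within simulation error. The no-penalty statement is right for these reviews.

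**Step 3: extension decided on by-arm data.** The protocol gives no rule, so one is assumed. Let planned events be 1 unit of information. An unblinded look at fraction t gives z₁. If |z₁| < 1.96, follow-up runs on to R times the planned events; otherwise the trial ends as planned. There is one final test at |Z| > 1.96, unadjusted, and no efficacy claim is made at an early look.

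Under the null, the statistic at R given z₁ is normal with mean z₁√(t/R) and variance (R − t)/R. The type I error is

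P(|z₁| < 1.96 and |Z_R| > 1.96) + P(|z₁| ≥ 1.96 and |Z₁| > 1.96),

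where Z_R and Z₁ are the final statistics with and without extension. Numerical integration gives:

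| Look at | R = 1.25 | R = 1.5 | R = 2 |
|---|---|---|---|
| 30% of planned events | 0.052 | 0.053 | 0.054 |
| 75% | 0.056 | 0.060 | 0.064 |
| Planned end | 0.071 | 0.077 | 0.083 |

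Simulation agrees to within 0.0002. If the extension were chosen in the most damaging way, up to R = 2, the values would be 0.058, 0.068 and 0.085.

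An extension of R = 1.25 is realistic. Under the planning rates with 21 months of enrolment, moving minimum follow-up from 9 to 15 months raises expected events from 60.5 to 77.9, a factor of 77.9/60.5 = 1.29.

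**Step 4: the sponsor's blind.** No arithmetic applies.
- 5.1.5: a non-voting Aeras member belongs to the SMC; the employment bar covers voting members only; the SMC is unblinded in its by-group reviews, with no exception.
- 7.6: Aeras is blinded to assignments and by-treatment interim results for the whole study.

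To satisfy both, the Aeras member would have to be kept out of the by-group material. Neither section says so.

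**The case against.** The case on the other side is substantial, and much of it limits the point.

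- A reader might infer that the protocol wrongly declares unblinded looks free of penalty. It does not. The sentence refers to the pooled reviews and is correct for them; on the later unblinded reviews the protocol is silent.
- A reader might infer that the SMC is to steer follow-up on by-arm results. The text permits unblinding but does not direct that use. Section 3.1 ties the end of follow-up to the last enrollee's 15-month visit, section 12 requires sponsor and IRB/IEC approval for any change, and 12.6 describes the one extension made as based on a pooled estimate. Even so, 7.6 still allows for extension, and in 5.1.5 the sponsor agrees to abide by the SMC's decision.
- The only review time stated is about 30% of expected events, where the inflation is small. This stands for the first review. Later reviews have no fixed time.
- A reader might infer that a sponsor employee sits in unblinded sessions. The text says only that an Aeras member records actions; it does not give that person's employment status or say which sessions are attended. Since 7.6 expressly asserts the blind, the defect is a contradiction without a stated safeguard, not proof of a breach.
- A reader might also object to this provision: "The statistical analysis plans to be prepared for all analyses will be approved by the SMC". Section 7 says only that the final plan is completed before database lock and unblinding. It does not say that this happens after the SMC's by-group reviews, so no change of approver is asked for.
- The SMC Charter and analysis plans are not at hand and may contain limits. That does not remove a discretion that the protocol itself grants, or a conflict between two of its own sections.

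**Conclusion.** The point holds in limited form. Section 7.6 permits by-arm unblinding for event-rate and endpoint purposes with no alpha provision and no bar on using the result to extend follow-up. If it were used that way, the two-sided error of the log-rank test would exceed 5%: barely for an early look (5.2–5.4%), modestly at 75% of planned events (5.6–6.4%), and materially at the planned end (7.1–8.3%). These figures rest on an assumed look time, an assumed extension of 1.25 to 2 times planned events, extension whenever the look is not significant, and an unadjusted final test.

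The conflict between 5.1.5 and 7.6 on the sponsor's blind rests on the text alone.

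Severity is moderate. Safety is the primary objective, and section 7.3 says the study is not designed as an efficacy study, so the 5% level at stake is that of a secondary test.

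**What to change.** In section 7.6, state that decisions on sample size and follow-up use pooled TB rates only and that SMC unblinding is reserved for safety. Alternatively, state that any view of TB by arm before an extension decision requires an alpha adjustment specified in advance.

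In section 5.1.5, state that the Aeras recorder attends open sessions only and has no access to by-group data or closed minutes. Carry both statements into the SMC Charter.

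The cost is wording. Sample size and power do not change, and pooled-only extension keeps the test at 5%. The downside is that the SMC loses the discretion to use by-arm data for questions of power.

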## 7.7 Interim Immunogenicity Review

The sponsor may conduct a review of immune response data prior to database lock after immunogenicity results are available for each of Study Groups 2, 3 and 4. Each Study Group will be analyzed individually. Blinded data will be available to investigators. Aggregate data will be presented at selected time points and will be presented identified only by a blinded label (e.g., 'Group A' and 'Group B').

Review of these data will allow the sponsor to determine if there is evidence of any immune response prior to completion of the trial. No decision cut points or stopping rules will be stipulated, no changes to monitoring practices or study procedures will be implemented following the reviews, and the study will continue following the reviews. No hypothesis testing will be performed.

Data summaries for preliminary immunogenicity review using blinded labels will be prepared by a statistician who is not the study statistician and who is not involved in study design, conduct, or analyses. Immunology technicians will perform all assays in a blinded manner. Data identified for inclusion in the immunogenicity summaries will be cleaned prior to statistical analysis; all statistical analysis programs used for the study will be validated prior to presentation of results.

### **7.8 Safety Reviews**

A blinded and unblinded-by-group review of safety data will be prepared for the SMC when the last subject in the Safety Cohort (Study Group 1) completes Study Day 84, and when the 1000th enrollee completes Study Day 84 as described in Section 5.1.5 and in the SMC Charter. Both blinded and unblinded analyses will be described in a statistical analysis plan, and unblinded reviews will be prepared for the SMC by an unblinded statistician not associated with the study conduct or primary analyses. All procedures associated with this review, including objectives, data handling, and elements to be included for review will be documented in the SMC minutes.

### **7.9 Final Study Report**

A final study report will be prepared after database lock is completed for all data collected through the final assessment of the study.

### **7.10 Computer Methods**

Statistical analyses will be performed using SAS® version 9.1 or later under a Windows operating system.

## **8 DATA COLLECTION, MONITORING, AND RECORD RETENTION**

For the purpose of monitoring and auditing the study, source documentation will consist of existing medical records and/or study records developed and maintained by the investigator. Any source document templates provided by Aeras or its designee will serve as supplements to the subject's study record.

Data recorded on source documents will be transcribed onto case report forms (CRF) provided by Aeras, or entered using electronic case report forms (eCRFs) using an Electronic Data Capture (EDC) system provided and approved by Aeras. Completed, original CRF will be retrieved by Aeras or its designee and a copy of each completed CRF (as applicable) will be retained at the clinical site as part of the study records.

The study will be monitored regularly by Aeras or its designee throughout the study period. For studies of unapproved investigational products, all study records (source documents, signed informed consent forms, copies of CRF (as applicable), IRB/IEC correspondence and approval letters, study vaccine management records) will be kept secured for a minimum of two years following the marketing of the investigational product or for 2 years after the discontinuation of the IND (or CTA, etc.). The investigator will ensure that study records are not disposed of or removed from the clinical site without prior notification and approval from Aeras or its designee.

## **9 HUMAN SUBJECTS**

### **9.1 Ethics and Regulatory Considerations**

The study will be conducted according to the Declaration of Helsinki, ICH-GCP, Protection of Human Subjects (21 CFR 50), Institutional Review Boards (21 CFR 56), Obligations of Clinical Investigators (21 CFR 312), and local regulatory requirements.

The protocol and informed consent form will be reviewed and approved by the IRB or IEC of each participating clinical site prior to any protocol-specified procedures being conducted. The investigator will inform the IRB/IEC as to the progress of the study on a regular basis, or at minimum, once a year. Aeras will also have an independent IRB review and approval of the protocol and informed consent form and will keep the IRB informed of the progress of the study.

Written informed consent will be obtained from each parent/guardian prior to any protocol-specified procedures being conducted.

To maintain confidentiality, subject identification numbers will be used to identify the subject's laboratory specimens, source documents, CRF, study reports, etc. All study records will be maintained in a secured location. Clinical information will not be released without written permission from the subject's parent/guardian except as necessary for monitoring or auditing of the study by Aeras or its designee or applicable regulatory authorities.

### **9.2 Institutional Review Board or Independent Ethics Committee**

All the documents the IRB/IEC may need to fulfill its responsibilities, such as the protocol, protocol amendments, information concerning subject recruitment, payment or compensation procedures, etc., will be submitted to the IRB/IEC by the investigator. The IRB's/IEC's written, unconditional approval of the study protocol and the informed consent form will be in the possession of the investigator/clinical site staff prior to the conduct of any protocol-specified procedures.

Modifications to the protocol may not be implemented without prior written IRB/IEC approval except when necessary to eliminate immediate hazards to the subjects or when the modification involves only logistical or administrative aspects of the study. Such logistical or

administrative modifications will be submitted to the IRB/IEC in writing by the investigator, and a copy of the correspondence to verify the submission will be maintained.

The investigator must inform the IRB/IEC of modifications to the informed consent or any other documents previously submitted for review/approval, of any new information that may adversely affect the safety of the subjects or the conduct of the study, provide an annual update and/or request for re-approval, and advise the IRB/IEC when the study has been completed.

Any documents or forms to be provided to the subject (e.g., information cards, form letters from the investigator), and all forms of study advertising (flyers, brochures, print advertisements, radio or television scripts, etc.) must be approved by Aeras or its designee prior to the clinical site submitting them to the IRB/IEC. Approval from the IRB/IEC must be obtained prior to providing the documents or forms to the subject.

### **9.3 Informed Consent**

The principles of informed consent in the current edition of the Declaration of Helsinki and 21 CFR 50.25 should be implemented prior to any protocol-specified procedures being conducted.

Informed consent will be documented in writing on a consent form approved by the IRB/IEC.

All relevant information should be provided in both oral and written form in a way that is understandable to the subject's parent/guardian. Ample time and opportunity must be given for the subject to inquire about details of the study. The written consent document will embody the elements of informed consent as described in the Declaration of Helsinki and will also comply with local regulations.

The investigator or the investigator's qualified designee will explain the nature of the study and inform the subject that participation is voluntary and that the subject can withdraw at any time.

The subject must be informed about the study's purpose including why the subject was selected to participate, study goals, expected benefits and risks, potential risks, and that some potential risks are unforeseeable. The individual must be provided with a description of the procedures and the estimated duration of time required for participation in the study, as well as alternative interventions or courses of treatment, if applicable.

The subject must receive an explanation as to whether any compensation and any medical treatments are available if injury occurs and, if so, what they are, where further information may be obtained, and who to contact in the event of a study-related injury. Individuals must be told who to contact for answers to any questions related to the study.

The subject must be informed that their participation is voluntary and that they are free to withdraw from the study for any reason at any time without penalty or loss of benefits to

which they are otherwise entitled. The extent of the confidentiality of subject records must be defined and the subject must be informed that applicable data protection legislation will apply.

The subject must be informed that the monitor(s), auditor(s), IRB/IEC members, and the applicable regulatory authorities will be granted direct access to the subject's original study medical records for verification of protocol-specified procedures and/or data, without violating the confidentiality of the subject to the extent permitted by the applicable laws and regulations. The subject must be informed that his/her signature on the informed consent form indicates that he/she has decided to participate in the study, having read and discussed the information presented.

Modifications made by the investigator to an informed consent form template provided to the investigator by Aeras or its designee will be reviewed and approved by Aeras or its designee prior to being submitted to the IRB/IEC.

The original, signed informed consent form for each subject will be maintained by the investigator as part of the subject's study records. A copy of the signed informed consent form will be provided to each subject.

